## Abstract

**Background:**

Accurate and timely patient handovers from hospital to other health care settings are essential in order to provide high quality of care and to ensure patient safety. We aim to investigate the effect of a comprehensive discharge bundle, the Transfer Intervention Procedure (TIP), on the time between discharge and the time when the medical, medication and nursing handovers are sent to the next health care provider. Our goal is to reduce this time to 24 h after hospital discharge. Secondary outcomes are length of hospital stay and unplanned readmission within 30 days rates.

**Methods:**

The current study is set to implement the TIP, a structured discharge process for all patients admitted to the hospital, with the purpose to provide a safe, reliable and accurate discharge process. Eight hospitals in the Netherlands will implement the TIP on one internal medicine and one surgical ward. An interrupted time series (ITS) analysis, with pre-defined pre and post intervention periods, will be conducted. Patients over the age of 18 admitted for more than 48 h to the participating wards are eligible for inclusion. At least 1000 patients will be included in both the pre-implementation and post-implementation group. The primary outcome is the number of medical, medication and nursing handovers being sent within 24 h after discharge. Secondary outcomes are length of hospital stay and unplanned readmission within 30 days. With regard to potential confounders, data will be collected on patient’s characteristics and information regarding the hospitalization. We will use segmented regression methods for analyzing the data, which allows assessing how much TIP changed the outcomes of interest immediately and over time.

**Discussion:**

This study protocol describes the implementation of TIP, which provides the foundation for a safe, reliable and accurate discharge process. If effective, nationwide implementation of the discharge bundle may result from this study protocol.

**Trial Registration:**

Dutch Trial Registry: NTR5951

## Background

Proper patient handovers from hospital to other health care providers are essential in order to provide high quality of care and to ensure patient safety. However, handovers are often delayed [1] and the patient is hardly involved in the discharge process [2, 3]. Besides, communication between secondary and primary care providers is known to be poor [1], clear treatment guidelines for hospital care and post-acute care are missing [4, 5], and healthcare professionals structurally prioritize acute care over post-acute care [6].

Patients are hence discharged with little coordination or follow-up and the transition between hospital and home reflects a vulnerable period. In fact, delays or errors in patient handovers can have serious consequences, including adverse drug events and readmissions within 30-days post-discharge [7].

Similar to the Unites States and England, attention is growing to reorganize and improve the discharge process in the Netherlands. Hospital stays are becoming shorter and an increasing numbers of older patients and chronically ill patients with chronic diseases and/or comorbidity require coordinated and continuous care [8].

Several studies have shown a positive effect, e.g. on readmission rates, of transitional care interventions, which often comprise a bundle of interventions for patients discharged from hospital to their home [9–11]. Yet, these are often comprehensive tailor-made interventions for high-risk patient populations, targeting patient-related factors, whereas cultural and other organizational aspects are important factors that form the basis to ensure the quality and safety of patient handovers for all patients [5]. Therefore, these aspects must be taken into account when interventions are developed. The current study is set to implement the Transfer Intervention Procedure (TIP), a structured discharge process for all adult patients admitted to an internal medicine or surgical ward, with the purpose to provide a safe, reliable and accurate discharge process to all patients.

### Objective

We aim to investigate the effect of a Transfer Intervention Procedure (TIP) on the time between hospital discharge and the time when the medical, medication and nursing handovers are being sent to the next health care provider. Our goal is to reduce this time to 24 h after hospital discharge for all patient handovers. Also, we aim to reduce length of hospital stay and unplanned readmission within 30 days rates.

## Methods

We adhere the SPIRIT guidelines for reporting of trial protocols [12] and all recommended items are addressed in the following paragraphs.

### Study design

An interrupted time-series (ITS) study will be conducted from March 2016 until June 2017. There will be six pre-implementation measurements and six post-implementation measurements with 1-month intervals. During the transition period, i.e. 2 months, implementation activities are set up and no measurements will be conducted. Figure 1 provides an illustration of the pre-implementation measurements, implementation period and post-implementation measurements.

**Fig. 1 Fig1:**
[figure not shown]
Interrupted Time Series

An ITS design is the strongest and most commonly used quasi-experimental design to evaluate the impact of an intervention or to measure the effects of a quality improvement when a randomized controlled trial is not feasible or there is no control over the implementation of an intervention [13, 14]. Randomizing implementation of the intervention in the participating hospitals is not possible in the current study, due to practical concerns of the hospitals. Therefore, ITS is chosen as an appropriate and powerful design by which outcomes before and after implementation of the TIP procedure will be compared, while accounting for potential confounders and potential data trends that occur without implementation of the intervention.

### Study setting

This study is embedded in the context of a larger working group of the Dutch Ministry of Health, Welfare and Sport: ‘Addressing Waste in Health Care’. ‘Addressing Waste in Health Care’ is set up in order to reduce inefficiencies in the provision of health care and services and to reduce health care expenditures, for example by reducing the number of preventable hospital readmissions. The implementation of TIP is one of the sub working groups of this larger national program. Eight hospitals (1 university medical center) in the Netherlands will implement the TIP procedure on one of their internal medicine wards and one of their surgical wards.

### The transfer intervention procedure

This study is set to implement the Transfer Intervention Procedure (TIP), which provides the foundation for a safe and reliable discharge process. We aim for a patient handover that is accurate and timely and also transparent to the patient. As previously described [15], a comprehensive discharge checklist may function as key element in standardizing the discharge process. A checklist, containing all elements of the TIP procedure, has to be completed in the patient’s medical record before hospital discharge in order to ensure that the steps will be undertaken. As described elsewhere [16], the TIP procedure was constructed based on focus group meetings with professionals, patient satisfaction surveys and literature. The TIP discharge bundle consists of four elements: 1) determining the discharge date within 48 h after admission and communication of the discharge date with the patient, 2) start with arrangement of required post-discharge care within 48 h after admission, 3) set up patient handover (medical, medication, nurse) and personalized patient discharge letter (PPDL) within 48 h after admission, 4) plan a discharge conversation with the patient to explain information from the PPDL 12 to 24 h before discharge.

### Implementation

The local project leader from the participating hospitals will develop a project plan for implementation of the TIP procedure in their hospital. If required, the study coordinator (RS) will help develop the project plan. All physicians, nurses and medical students involved in patient care on the participating wards will be targeted and motivated to ensure implementation. The plan will include standard items, such as education, reminders and feedback sessions with other participating hospitals, and, if required, local additional items. Table 1 provides an overview of the activities to stimulate implementation of the TIP discharge bundle.

**Table 1 Tab1:** Description of activities to enhance implementation of TIP

Activity	Aim	Period	For whom	How
Providing information to hospitals about the TIP	Creating awareness Motivating Explanation of TIP procedure Providing background information	At start of implementation period	Project leader Physicians Nurses	Presentation
Patient-education	Creating awareness Patient involvement	During whole implementation period	Patients	Flyers
Results reporting with competitive feedback session	Motivation Awareness of current competition Sharing of experiences with regard to facilitators and barriers of implementation	During whole implementation period	Project leader Physicians Nurses	Presentation Feedback session

### Primary and secondary outcomes

The primary outcome is the number of medical, medication and nursing handovers being sent within 24 h after discharge. Secondary outcomes are length of hospital stay unplanned readmission within 30 days rates.

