### Data collection

Variables concerning the primary and secondary outcomes with possible confounders will be collected (see Table 2). These data will be collected from the patient’s medical file and the discharge summary. Castor Electronic Data Capture (EDC) will be used to build electronic Case Report Forms (eCRFs) for save and valid data collection.

**Table 2 Tab2:** Overview of data collection procedure

	Instrument or Question	Source
Demographical data		Medical record
Age		
Gender		
Socioeconomic status	Postal code	
Marital status		
Living arrangement	e.g. independent, nursing home, sheltered housing.	
Hospitalization		Medical record
Ward	Internal/Surgical	
Index-diagnosis	Acute/Planned	
Length of hospital stay	Time between admission and discharge	
Medical data		Medical record
Presence of polypharmacy	Does the patient uses five or more different medications?	
Comorbidity	Charlson Comorbidity Index [20]	
Number of hospitalizations during six months prior to current hospital stay		
Duration of patient handovers	Time in hours between discharge and the medical, medication and nursing handovers	Medical record
Readmissions	Number of unplanned readmissions within 30 days	Medical record
Emergency department visits	Number of emergency department visits within 30 days	Medical record

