### Patients and sample size

All patients over the age of 18 admitted for more than 48 h to one of the 16 participating wards of the eight participating hospitals are eligible for inclusion. The aim is to include at least 22 patients at each time point in all participating hospitals; 11 patients from an internal ward and 11 patients from a surgical ward. With a total of six time points, this will result into at least 65 patients per ward. Hence, we will include at least 1000 patients in the period prior implementation (baseline group) and 1000 patients in the period after the implementation (intervention group). This number is based on the number of hospital beds at the participating wards and feasibility with regard to data collection. We conducted a power analysis with this number of patients, which is based on the findings of a previous study [16]. However, we expect to find a greater effect in the current study, namely a reduction of 78 % in the time of patient handovers being sent to the next health care provider. In a simulation study with 16 wards, each contributing 65 patients, we estimated the power to be approximate 91 % to demonstrate a reduction of 78 % in time until sending the medical discharge letter, assuming that the intraclass correlation coefficient does not exceed 0.05.

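### The objective, planned effect and collected data are in hours to handover, but the primary outcome is the number sent within 24 h and hours are not a named outcome

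*Protocol article*

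**What the plan says.** The Objective section of the protocol article names the quantity that TIP is meant to change: "the time between hospital discharge and the time when the medical, medication and nursing handovers are being sent to the next health care provider". It adds a target: "Our goal is to reduce this time to 24 h after hospital discharge for all patient handovers". Table 2 (Data collection) records "Time in hours between discharge and the medical, medication and nursing handovers". The sample-size section plans for an effect on the same scale, "namely a reduction of 78 % in the time of patient handovers being sent to the next health care provider", and gives its power on that scale for one of the three handovers: "we estimated the power to be approximate 91 % to demonstrate a reduction of 78 % in time until sending the medical discharge letter".

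The section Primary and secondary outcomes, like the Methods part of the abstract, then states: "The primary outcome is the number of medical, medication and nursing handovers being sent within 24 h after discharge". The secondary outcomes are length of stay and unplanned readmission within 30 days. Time to handover is in neither list. The Discussion repeats the aim that all handovers go out within 24 h.

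**The concern.** The question, the planned effect, the power statement and the data are on one scale, and the outcome that will carry the conclusion is on another. The primary outcome registers only movement across 24 h. A shortening that stays on one side of that limit leaves it unchanged, however large. The primary result would therefore not estimate the quantity in the objective, and no other listed outcome would either. Reducing a recorded time to yes or no also loses information, so the same records may yield less power on the 24 h scale than on the hours scale. The article gives no power for the 24 h outcome.

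**Working it through.** **1. The passages side by side**

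| Element | Where | Scale |
|---|---|---|
| Objective | Objective | hours |
| Goal | Abstract, Objective, Discussion | 24 h limit |
| Collected variable | Table 2 | hours |
| Planned effect | Patients and sample size | 78% reduction in hours |
| 91% power | Patients and sample size | hours, medical letter only |
| Primary outcome | Abstract, Primary and secondary outcomes | number within 24 h |
| Secondary outcomes | same | stay, readmission |

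**2. What the cut does to the planned effect**

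A 78% reduction multiplies a time by 0.22. The result is below 24 h only if the original time is below 24/0.22 = 109 h. A handover at 200 h moves to 200 × 0.22 = 44 h and is late before and after.

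Illustration (assumed: log-normal times, baseline median 168 h, every time cut by 78%). With log SD 1, 1.5 and 2, the share within 24 h goes from 2.6% to 33.3%, 9.7% to 38.7% and 16.5% to 41.5%. Of the handovers late at baseline, (1 − 0.333)/(1 − 0.026) = 68%, and likewise 68% and 70%, stay late.

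**3. The plan's own 91%**

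Inputs from the article: ratio 0.22, 16 wards × 65 = 1040 patients, ICC at most 0.05, six monthly points before and six after with a two-month gap. Not given: alpha, SD, baseline times, simulation model. Assumed here: two-sided 5%, log-normal times, and 65 patients per ward in each period.

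- Log effect: −ln(0.22) = 1.514. Distance needed for 91% power: 1.960 + 1.341 = 3.301.
- Simple before-after comparison: design effect 1 + 64 × 0.05 = 4.2, effective n = 1040/4.2 = 247.6 per period. The log SD that gives 91% is 1.514/(3.301 × √(2/247.6)) = 5.1.
- Segmented model (months 1–6 and 9–14, level change at month 9): variance factor 2.419, 1040/6 = 173.3 patients per month. The log SD that gives 91% is 1.514/(3.301 × √(2.419/173.3)) = 3.9. With a design effect of 4.2 it is 1.9. With 65 per ward in total rather than per period, it is 1.3.

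The 91% can be neither confirmed nor refuted. It fits log SDs from about 1.3 to 5.1, depending on model and clustering.

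**4. Power on the 24 h scale if 91% is taken as given**

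For a small shift in log-normal times, a cut with share p below it keeps the fraction φ(z_p)²/[p(1−p)] of the information. Power is Φ(√fraction × 3.301 − 1.960).

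| Share within 24 h | Fraction kept | Power |
|---|---|---|
| 50% | 0.637 | 75.0% |
| 20% or 80% | 0.490 | 63.7% |
| 14% or 86% | 0.411 | 56.2% |
| 10% or 90% | 0.342 | 48.8% |
| 5% or 95% | 0.224 | 34.5% |

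Using the full shift of 1.514/5.1 = 0.30 SD in the simple comparison gives 54%, 67%, 75%, 59% and 42% at baseline shares of 10%, 20%, 50%, 80% and 90%.

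**5. Power if a log SD of 1 to 2 is assumed instead**

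Segmented level change, baseline medians 24 to 336 h:

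- No design effect: power on hours is about 100%. Power on the 24 h cut is at least about 99%, a loss of about 0 to 1 point.
- Design effect 4.2, log SD 2: power on hours is 88%. Power on the cut is 53 to 68% with a pooled variance and 65 to 74% with separate variances before and after.

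**The case against.** The strongest reply is that 24 h is not an arbitrary cut. It is the declared goal in the abstract, the Objective and the Discussion, and for a quality-improvement bundle the share meeting the standard is legitimate and easily read. A handover that moves from 200 h to 44 h still fails that standard. This stands: the 24 h share belongs in the report, and the absence of an external guideline for it is no error. It does not explain why the time named in the objective is missing from both outcome lists.

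A reader might infer that the cut costs 16 to 35 points of power, or that the trial would probably miss its expected effect. The documents support neither. The 16 to 35 points arise only if 91% is accepted, times are log-normal and the share within 24 h lies between about 14% and 86%. In a segmented model without a design effect, that also needs a log SD of about 3.9. Such an SD implies a 95% range of exp(1.96 × 3.9), about 2,088-fold either side of the median: for a 24 h median, under a minute to more than five years. At log SD 1 to 2 without a design effect, both scales detect the effect almost surely, even when delays run to several days. The larger losses at those SDs depend on applying the full design effect of 4.2 to a comparison made largely within wards, which is a severe assumption.

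Hours also bring a difficulty of their own. Because handovers are to be set up within 48 h of admission, some may be sent at or before discharge, and a log of hours needs a rule for zero or negative times.

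**Conclusion.** The mismatch is firm and rests on the article's text alone: objective, planned effect, power and data are in hours; the primary outcome is a count within 24 h; and no listed outcome estimates the objective. The 109 h limit is simple arithmetic on the stated 78%.

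The loss of power is conditional. It runs from about 0 points (log SD 1 to 2, no design effect) to more than 50 (91% taken as given, with a share of 5% or 95% within 24 h). No single figure should be quoted as a property of this plan. The conclusion does not need one: even with ample power, the 24 h count answers whether a standard is met more often, not by how much handover time falls. The point should be acted on, because the missing outcome is the one the trial says it is about and its data are already collected.

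**What to change.** In Primary and secondary outcomes and in the abstract, make hours from discharge to sending the handovers the primary outcome. This matches the objective and puts the primary analysis on the scale of the power statement. Analyse it at patient level in the segmented model on a time scale, for example log hours or a time-to-event model. Fix in advance a censoring horizon for handovers never sent and a rule for those sent at or before discharge. Keep the proportion sent within 24 h as the first secondary outcome, because it is the project's declared target.

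At the least, if the 24 h outcome stays primary, name hours as the key secondary outcome.

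Cost: wording, a time-scale model and the two handling rules; no new patients or data. The downside is that the headline becomes a ratio of times, which is less easily read than a share within 24 h.

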### Data collection

Variables concerning the primary and secondary outcomes with possible confounders will be collected (see Table 2). These data will be collected from the patient’s medical file and the discharge summary. Castor Electronic Data Capture (EDC) will be used to build electronic Case Report Forms (eCRFs) for save and valid data collection.

**Table 2 Tab2:** Overview of data collection procedure

	Instrument or Question	Source
Demographical data		Medical record
Age		
Gender		
Socioeconomic status	Postal code	
Marital status		
Living arrangement	e.g. independent, nursing home, sheltered housing.	
Hospitalization		Medical record
Ward	Internal/Surgical	
Index-diagnosis	Acute/Planned	
Length of hospital stay	Time between admission and discharge	
Medical data		Medical record
Presence of polypharmacy	Does the patient uses five or more different medications?	
Comorbidity	Charlson Comorbidity Index [20]	
Number of hospitalizations during six months prior to current hospital stay		
Duration of patient handovers	Time in hours between discharge and the medical, medication and nursing handovers	Medical record
Readmissions	Number of unplanned readmissions within 30 days	Medical record
Emergency department visits	Number of emergency department visits within 30 days	Medical record

### Patients and sample size

All patients over the age of 18 admitted for more than 48 h to one of the 16 participating wards of the eight participating hospitals are eligible for inclusion. The aim is to include at least 22 patients at each time point in all participating hospitals; 11 patients from an internal ward and 11 patients from a surgical ward. With a total of six time points, this will result into at least 65 patients per ward. Hence, we will include at least 1000 patients in the period prior implementation (baseline group) and 1000 patients in the period after the implementation (intervention group). This number is based on the number of hospital beds at the participating wards and feasibility with regard to data collection. We conducted a power analysis with this number of patients, which is based on the findings of a previous study [16]. However, we expect to find a greater effect in the current study, namely a reduction of 78 % in the time of patient handovers being sent to the next health care provider. In a simulation study with 16 wards, each contributing 65 patients, we estimated the power to be approximate 91 % to demonstrate a reduction of 78 % in time until sending the medical discharge letter, assuming that the intraclass correlation coefficient does not exceed 0.05.

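### Because only stays above 48 h are sampled, a TIP effect that moves discharges to before 48 h would be partly hidden in the length-of-stay comparison

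*Protocol article*

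**What the plan says.** - **Eligibility** (Protocol article, Patients and sample size): "All patients over the age of 18 admitted for more than 48 h to one of the 16 participating wards". The Abstract repeats the 48 h condition.
- **Outcome** (Primary and secondary outcomes): "Secondary outcomes are length of hospital stay unplanned readmission within 30 days rates". Table 2 under Data collection defines length of hospital stay as "Time between admission and discharge".
- **Aim** (Objective): "Also, we aim to reduce length of hospital stay and unplanned readmission within 30 days rates". No size is given for either reduction.
- **Timing of the intervention** (The transfer intervention procedure): the first element is "determining the discharge date within 48 h after admission and communication of the discharge date with the patient" and the second is "start with arrangement of required post-discharge care within 48 h after admission". The third, setting up the handover and the patient letter, has the same 48 h limit. Only the fourth is tied to the end of the stay: "plan a discharge conversation with the patient to explain information from the PPDL 12 to 24 h before discharge".
- **Who receives TIP**: the Abstract and Background describe it as a process for all admitted (adult) patients, not only those who stay beyond 48 h.
- **Analysis**: segmented regression for level and slope change, fitted to the included patients. The article describes no count of admissions that fail the 48 h condition.

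**The concern.** The quantity that decides who is sampled is the quantity tested as an outcome, and most of the intervention is due before a patient can be known to qualify. A stay that would have lasted a little over 48 h counts in the pre-implementation months. If TIP shortens such a stay to 48 h or less, the patient is missing from the post-implementation months. The shortest eligible stays are thinned out after implementation only, which raises the post-implementation mean and works against the reduction being sought.

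The change in selection would coincide with implementation, so it would enter the level change that the segmented regression estimates. Covariate adjustment and the correction for autocorrelation act on included patients and cannot restore absent ones. Recruitment counts would not show the shift either, because they follow a target of 11 patients per ward and time point.

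At stake are the two named secondary outcomes. The Discussion says nationwide implementation may follow, and Study setting places TIP in a programme to cut expenditure and readmissions, so an understated length-of-stay effect could mislead that decision.

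**Working it through.** **The plan's own figures.** 11 patients × 6 time points = 66 per ward, and 16 wards × 65 = 1,040 per period. Both agree with the stated minima of 65 and 1,000. The power of about 91 % concerns time to sending the medical discharge letter. It cannot be reproduced without the SD, alpha and simulation model, and this point does not depend on it.

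**Inputs.** From the protocol: the cut at 48 h (2 days), applied in both periods. Assumed, because the protocol gives neither: the distribution of stays and the TIP effect on them. Stays are taken as log-normal with median 3, 4, 5 or 6 days and log-SD *s* = 0.7, 0.8 or 0.9 (12 combinations). The true effect is the change in patients who would have stayed more than 2 days without TIP. The observed effect compares the mean of stays above 2 days before with the mean of stays above 2 days after.

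**Formula.** With μ = ln(median), the mean of stays above a cut *c* is

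m(c) = exp(μ + s²/2) × Φ((μ + s² − ln c)/s) / Φ((μ − ln c)/s).

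**1. Every stay shortened by 15 %.** A stay remains eligible only if it would have exceeded 2/0.85 = 2.353 days, so the post mean is 0.85 × m(2.353). For median 4 and *s* = 0.8:
- Pre: m(2) = 5.509 × 0.952/0.807 = 6.50 days.
- Post: 0.85 × (5.509 × 0.928/0.746) = 0.85 × 6.85 = 5.82 days.
- Observed reduction: 1 − 5.82/6.50 = 10.4 % (0.68 day), against a true 15 % (0.15 × 6.50 = 0.98 day).
- Share of admissions at or below 48 h: 19.3 % before, 25.4 % after.

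Over the 12 combinations the observed reduction is 8.9-12.8 %, and the share at or below 48 h rises by about 3-8 percentage points.

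A separate set of assumptions (exponential with mean 5 or 7 days; log-normal with median 3-5 days and log-SD 0.8, or median 6 days and log-SD 0.6) gives the same pattern. A true 10 % appears as 6.0-9.0 %, and a true 20 % as 11.8-17.7 %.

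**2. Every stay shortened by half a day.** The observed change is m(2.5) − 0.5 − m(2). For median 4 and *s* = 0.8 it is 0.00 day. Over the 12 combinations it runs from −0.19 to +0.12 day, against a true −0.50 day.

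**3. Only time beyond 48 h shortened.** No stay crosses the cut, so the same patients are compared and the observed and true reductions are equal. The bias is zero.

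**4. Readmission, with no true TIP effect.** Assumed risk: logit = −2.4 + 0.5 × ln(stay without TIP in days / 4), which gives about 9-11 % before implementation. Under the separate set of distributions in step 1, the post-implementation rate appears 0.1-0.2 percentage points higher with a 10 % shortening and 0.2-0.5 points higher with 20 %. For scale, the standard error of a difference near 10 % with 1,040 per period is √(2 × 0.10 × 0.90/1,040) = 1.3 points before any allowance for clustering.

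**The case against.** The strongest reply is that bias is possible but not shown. It needs discharges to move across the 48 h line, and the protocol reports no crossing rate, length-of-stay effect or distribution. The 48 h in the TIP description is a deadline. The early elements are planning steps that could be done at hour 47, and nothing says they produce discharges before 48 h. The cut may also have a sensible purpose: the compliance indicators under Validation and process evaluation use a 48 h window, which can be fully observed only in patients still in hospital then. That purpose is an inference, since the article gives none. Table 2 also collects comorbidity, polypharmacy, earlier hospitalisations and acute or planned status, which address part of a case-mix shift.

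Much of this stands, and it rules out several stronger readings that a reader might infer:
- *That both secondary effects are biased.* Step 3 shows a plausible case with no bias.
- *That TIP acts from the moment of admission.* The text sets only a 48 h limit.
- *That the length-of-stay effect will reverse sign.* Clear reversal needs an effect confined to short stays. If only stays under 4 days were cut by 20 % (median 4, log-SD 0.8), a true −3.4 % would appear as +4.7 %. Nothing in the article supports that pattern. A uniform percentage cut did not reverse in any combination tried, and a fixed half-day cut is at most slightly reversed.
- *That readmission is materially inflated.* The shift is under half a standard error and assumes that risk rises with length of stay.
- *That the main result is compromised.* Handovers sent within 24 h of discharge do not determine eligibility.

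What remains is that the design, as described, cannot tell the harmless case from the harmful one, because it collects nothing on stays of 48 h or less.

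**Conclusion.** The point holds as a risk of selection bias in the length-of-stay comparison, most likely toward no effect, with a possible small upward shift in readmission. The structure is in the protocol's own text: the sample is cut on a tested outcome, and most of the intervention is due before the cut. The size is not in the text. Under the assumed log-normal stays, a uniform 15 % shortening would appear as about 9-13 % and a uniform half-day cut would be mostly or wholly erased; the bias is zero if no stay crosses 48 h. The primary outcome and the power statement are not affected. This is an inexpensive improvement to the secondary analyses, not a flaw that invalidates the trial.

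**What to change.** 1. Keep the chart sample of stays above 48 h for the handover outcomes.
2. Analyse length of stay in all adult admissions to the 16 wards, from admission and discharge dates with no minimum stay, at least as a sensitivity analysis beside the analysis above 48 h. Do the same for unplanned 30-day readmission where it can be identified.
3. Report the monthly number and share of stays of 48 h or less per ward as a separate series, to show whether eligibility shifted at implementation.
4. If that share shifts, or the data cannot be obtained, limit the length-of-stay and readmission conclusions accordingly and state the risk of selection bias.

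**Cost.** One administrative extract per hospital. Its availability, and whether it can separate unplanned from planned readmissions, are assumptions, because Table 2 names only the medical record as a source. Patients outside the chart sample would lack the chart-collected covariates, so these analyses would carry less confounder adjustment. They would also describe a wider population than the primary outcome does, which the report should say.
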